## Methods/design

The following methodology is in full agreement with the SPIRIT (Standard Protocol Items for Randomized Trials) recommendations [45–47] and the Osteoarthritis Research Society International (OARSI) recommendations for RCTs [48] to ensure methodological rigor. Consolidated Standards of Reporting Trials (CONSORT) [49] guidelines will be followed for reporting on the results in a subsequent article.

### Study design

The study is a single blind, two-arm RCT with a parallel group design to compare two study groups: 1) a knitting intervention (Group 1) and 2) a waiting list control group (Group 2). The intervention period will be 12 weeks plus a follow-up at 4 weeks post-intervention to measure the retention effect. Since this RCT involves a physical intervention (i.e. knitting program), the therapist, participants, and research coordinator administering the program will not be blinded. A blinded independent assessor will be trained to assess the participants though performance evaluation and self-reported questionnaires given at baseline, 3,6,9,12-week as well as at 4-week follow-up to reduce detection bias. With training and standard operating procedures, it is anticipated that any performance bias due to unblinding will be minimized. The study design flow chart is presented in Fig. 1. The study protocol is approved by the University of Ottawa Research Ethics Board (#H02–16-12).

**Fig. 1 Fig1:**
[figure not shown]
Study design flow chart

### Study population

The diagnosis of HOA will be made by a rheumatologist ([name]) and will be consistent with the clinical criteria as set out by the American College of Rheumatology (ACR) classification of HOA [50], the radiologic criteria according to Kallman et al. [51] (1989), and the disease activity criteria according to the Doyle Articular Index [52]. The severity of the HOA will be determined according to ACR classification of HOA and by clinically assessing the presence of (1) pain, aching or joint stiffness, (2) bony enlargement of 2 or more of 10 selected finger joints, (3) bony enlargement of at least a distal interphalageal (DIP) joint, and (4) fewer than 2 swollen metacarpophalageal (MCP) joints, or (5) deformity of at least 1 of 10 selected joints. Presence of OA will be confirmed by a recent X-rays taken of each hand (less than 1 year); films will be interpreted by a radiologist and reports will be sent to the rheumatologist ([name]) to confirm diagnosis and classification.

### Inclusion/exclusion criteria

To be eligible for this RCT, participants will be required to: 1) meet the ACR clinical and radiographic criteria of definite HOA and of mild to moderate severity status [50] and have experienced pain symptoms for at least 3 months, 2) be between 50 and 85 years of age, 3) have a level of morning stiffness of at least 4/10 on a visual analogue scale (VAS) [53] at the time of study entry, 4) display X-ray evidence of joint space narrowing of the hands [51], 5) have no knowledge of knitting (do not know how to knit) or have not knitted in the last 2 months; 6) be available for sessions at the senior’s club twice a week, 7) be able to understand written and verbal English instructions. Participants will be excluded if they: 1) are current active knitters; 2) are unwilling or unable to adhere to the knitting program for 12 consecutive weeks, 3) have other orthopedic, rheumatologic diseases (i.e. inflammatory arthritis, psoriasis arthritis, gout…), or evidence of chondrocalcinosis, 4) had any prior surgery for the finger joints, 5) have any acute disease, such as uncontrolled diabetes mellitus, untreated hypertension, neurological deficits (motor or sensory) or cognitive deficit and mental health conditions, 6) are taking OA medication that is expected to change during the study period, 7) receiving current rehabilitation treatment or any other pain-related treatment besides medication for OA, 8) have received corticosteroid injection of finger joints within the last 6 months, 9) plan to move or relocate within 6 months.

### Recruitment

Three main methods will be used to recruit potential participants. Advertisements in local newspapers will be placed. Information letters will be sent to local rheumatologists and posters will be placed in waiting rooms of each different Ottawa-based rheumatology units and TAS office. Potential participants will be invited to complete an online eligibility/admission questionnaire [53], including sociodemographic, initial intensity, location (e.g. finger joints versus thumb joints; right versus left hand), timing, intensity and duration of morning stiffness and pain [54–56] and handedness information [57, 58] to ensure that they meet the study’s selection criteria prior to randomization. If deemed eligible, participants will be invited to meet the research coordinator to confirm eligibility, sign an informed consent form, and complete baseline evaluations. In a previous RCT on HOA [59], 40 participants over 3 months were recruited, thus the data collection involving a 12-week knitting program for each participant should represent approximately six additional months, leaving 2 months for data analysis and writing the scientific report.

### Group assignment

Eligible participants will be randomly assigned to each group (ratio1:1). Participants of group 2 will have access to the knitting program after the completion of the RCT. Central randomization [60] based on a sequence of computer-generated random numbers (using statistical software SAS macro in SAS 9.3) using a blocking factor (randomly varying between 4 and 6) will be used.

The research coordinator, who is not involved in data collection, will contact the research study Methods Center data manager. Prior to running the randomization program, the data manager will document the participant’s initials (first and last) and date of birth (month and year). After running the program, the data manager will document the intervention assignment with the participant information, assign a study identification (ID) and then inform the research assistant of the assignment and participant ID. This process will help ensure concealment of allocation. After randomization, the participant will be informed of their group assignment.

### Intervention

Participants in both groups will continue with their on-going medical care To measure the true effect of the knitting intervention, active hand exercises need to be avoided since they are proven effective for HOA [7, 9–16, 61]. This may not be possible thus all participants will complete a daily activity log.

Participants in **Group 1** will take part in a low-intensity knitting program, performed as a morning functional activity, which will comprise two components: 1) bi-weekly 20-min knitting sessions at a senior’s club and 2) 20-min home daily knitting sessions for the five remaining weekdays over 12 consecutive weeks (total of 90 sessions). The bi-weekly 20-min knitting session will take place, at **a Senior’s Club in metropolitan Ottawa,** on Tuesday and Thursday mornings with a group of regular members who knit wool blankets for sick children admitted CHEO, a regional Children’s Hospital. The blankets are composed of individual squares that are assembled together. Each wool square takes approximately 20 min for a beginner knitter. Each knitter will be encouraged to knit one wool square per day for a total of seven squares per week. To avoid excessive isometric strength and potential muscle fatigue with the use of small needles that require precise pinching, participants will use specific knitting needle and wool sizes (sizes #6 and #5 respectively according to the Standard Yarn Weight System (**http://www.craftyarncouncil.com/weight.html**). Study participants will learn how to knit with a qualified instructor from Senior’s Club during the knitting sessions which will also be supervised by a trained OT to ensure that the physiological and clinical characteristics of therapeutic exercise are being met. A knitting instructor will ensure that participants follow the prescribed program and if their individual logbooks, where they recorded their daily hand activities and morning stiffness and pain levels, are filled properly. In the event that a session is missed, participants in Group 1 will receive a telephone reminder from the research assistant to encourage them to attend the next session. At the end of 12 weeks, participants will be encouraged to continue on with the program if they gained an improvement of their condition.

Participants assigned to the control group (Group 2) will be placed on a waiting list until the end of the study (12 weeks) plus the 4-week follow-up period. The research coordinator will offer one introductory session to explain how to record any activity in their logbooks as well a weekly telephone follow-up by the coordinator to if participant understood well how to fill them daily. Participants will not be permitted to attend knitting sessions at the senior’s club during the study duration. After the completion of the study duration, the knitting sessions will be available to all study participants. To avoid potential contamination, individuals in Group 2 will have no contact with the individuals registered at Senior’s Club in Group 1. Club membership annual fees ($10/year) will be paid for all study participants in Group 1 and for those in Group 2 only after the completion of the study. Free knitting material and lessons will be provided for all study participants.

### Self-reported and performance-based clinical outcomes outcome measures (Table 1)

The clinical outcomes were selected according to the OMERACT framework illustrated in Fig. 2 and include the followings:

**Table 1 Tab1:** Assessment schedule for primary, and secondary outcome measures

Assessment	Admission	Daily	Baseline	3/6/9 weeks mid intervention	12 weeks end of intervention	4 weeks follow-up
Informed consent (pre-admission)	X					
Diagnosis of HOA based on ACR criteria	X					
Socio-demographics	X					
Edinburgh Handedness Inventory	X					
Self-reported daily morning stiffness intensity (Visual analogue scale: VAS) (primary daily outcome)	X	X	X	X	X	X
Self-reported daily pain intensity (VAS) (intermediate daily outcome)	X	X	X	X	X	X
Pain intensity (Auscan) (periodic secondary measurement)			X	X	X	X
Morning stiffness severity (Auscan) (periodic secondary outcome)			X	X	X	X
Hand functional status/difficulty in activities of daily living (Auscan) (periodic secondary outcome)			X	X	X	X
Disease activity status (periodic secondary outcome)			X	X	X	X
Dynamometric strength measurements (Grip and pinch measurements) (periodic secondary outcome)			X	X	X	X
The Functional Index for Hand Osteoarthritis (FIHOA) (periodic secondary outcome)			X	X	X	X
Hand physical activity level (periodic secondary outcome)		X	X	X	X	X
Patient global assessment (periodic secondary outcome)			X	X	X	X
Quality of life (EQ-5D) (periodic secondary outcome)			X	X	X	X
Self-efficacy (periodic secondary outcome)			X	X	X	X
Physical Activity Enjoyment Scale (PACES) (Group 1 only)				X	X	X
Adherence to knitting program (Daily secondary outcome)			X	X	X	X
7-day Physical Activity Recall (PAR) (Daily secondary outcome)			X	X	X	X

**Fig. 2 Fig2:**
[figure not shown]
Preliminary set of endorsed core domains for hand osteoarthritis studies. Inner circle: Domains for all settings, i.e., clinical trials of symptom modification, clinical trials of structure modification, and observational studies. Outer circle: Domains for some settings, i.e., clinical trials of structure modification and observational studies. *Domains not mandatory as long as no disease-specific instruments are available. HR: health-related. “Reprinted with permission from The Journal of Rheumatology, Kloppenburg, M., et al J Rheumatol 2015; All rights reserve” ©2015

### Self-reported clinical outcomes (Table 1)

**Morning stiffness and pain relief**, using daily visual analogue scale for morning stiffness (primary outcome) and for pain (secondary outcome) will be recorded before (baseline) and after knitting (immediately, 2 h and 4 hours after the 20-min knitting daily morning activity). Daily morning stiffness after 2 h knitting daily morning activity will be our primary outcome measure of this protocol. This choice of primary and intermediate outcomes is based on the feasibility study conducted by the team.

**Functional status**, using Australian/Canadian Osteoarthritis Hand Index (AUSCAN) tool as a validated, reliable and responsive measurement scale for HOA [62–64] was adopted. The AUSCAN includes a 15-item scale, with items grouped into three sub-sections: A) pain intensity, B) stiffness severity and C) hand functional status/difficulty in activities of daily living. It uses a five-point scoring system. A score of 0 represents no pain or no severity in stiffness or no difficulty in performing functional tasks; scores between one and four represent mild to extreme gradations, respectively. Morning stiffness and hand functional status are included in the AUSCAN.

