## Abstract

**Background:**

The prevalence of hand osteoarthritis (HOA) has been reported to be higher amongst women over 50 years old (66%) compared to men of the same age (34%). Although exercise therapy has been shown effective in reducing symptoms and disability associated with HOA, adherence to treatment programs remains low. The primary objective of this RCT is to examine the effectiveness of a 12-week knitting program for morning stiffness (primary outcome) and pain relief (secondary outcome) 2 h post-wakening in females (aged 50 to 85 years old) with mild to moderate hand osteoarthritis (HOA).

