The proposed knitting program is based on: 1) evidence stemming from physiological studies [34–36]; 2) recommendations for individuals over 50 years old with OA [37] and specifically with HOA [12]; 3) evidence-based general exercise protocols for HOA [5, 38, 39] and OA of the thumb [40–42]; 4) current RCTs on therapeutic exercises for HOA [9, 14] and on the case study parameters described above [43]. In the proposed study, knitting will be a low-intensity hand exercise therapy comprising bilaterally dynamic and isometric movement of fingers, thumbs and wrists. Despite knitting being endorsed by The Arthritis Foundation [44] devoted to arthritis as a therapeutic activity for adults living with HOA, to our knowledge, no other comparative study studied its effectiveness on reducing symptoms related to HOA, potentially decreasing their impact in daily life and thus improving quality of life.

The primary objective of this RCT will be to examine the effectiveness of a 12-week knitting program for morning stiffness (primary outcome) and pain relief (secondary outcome) for participants in the knitting in Group 1 compared to participants in the control group assigned to a waiting list (Group 2) in older females (aged 50 to 85 years old) with mild to moderate osteoarthritis of the hands (HOA) after 2 h post-awakening. The secondary objective is to determine if older females with mild to moderate HOA using an adapted knitting program (Group 1) have improved hand and finger strength and physical function, self-efficacy, hand physical activity level and adherence, global patient improvement as well as quality of life (QoL) compared to a waiting list control group (Group 2) over 12 weeks of intervention and after a follow-up at 4 weeks post intervention. Our general hypothesis is that older females with mild to moderate HOA in the 12-week knitting group (Group 1) will have significant improvements in all daily clinical and implementation outcomes compared to the participants in the waiting list (Group 2) after 12 weeks of intervention.

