**Hand activity**
***level***, using an adapted 7-Day Physical Activity Readiness (PAR) [65–67] was used. The 7-day PAR is a validated instrument in a calendar format in which a participant can indicate the PA duration (minutes per day) and PA frequency (days per week). An adapted version of the 7-day PAR will be included in the logbooks where physical activity is split into distinct Knitting and other hand activities categories. The logbooks will also include a daily visual analogue scale for morning stiffness and pain intensity before and after knitting, information about hand physical activity level and knitting technique as well as a weekly questionnaire on actual changes in PA, medication intake (not encouraged), habits and adverse events. A similar logbook was created for PA activity other than knitting recording for the participants in the control group 2. ***Patient global assessment*** will be evaluated by asking patients if their condition after knitting program “fully improved”, “partially improved”, “did not improve” or “was worse compared to the beginning of the study” [31]. ***Health-related QoL*** will be assessed using the EuroQoL Index (EQ-5D-5 L) [68] including mobility, self-care, usual activities, pain/discomfort and anxiety/depression subscales.

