### Statistical analysis

Descriptive statistics will be used to summarize the study variables and to assess the distributional assumptions of the statistical techniques used. An intention to treat analysis will be conducted for all the data analyses.

A per protocol analysis will be considered as part of the sensitivity analyses. The primary outcome is the area under the curve (AUC) at 2 h for stiffness. That is, stiffness at 2 h post-awakening from sleep will be assessed each day for 12 weeks, and the AUC over this 12 week period will then be calculated. Similar AUCs will be calculated for stiffness at 0 h (at awakening), 4 h (post-awakening) and evening. Also, similar AUCs for the secondary outcomes pain and function will be calculated.

For the primary outcome (AUC at 2 h for stiffness) participants in the knitting group will be compared to participants in the control group using independent Student’s t-test with the pooled or separate variance estimate as appropriate. For the primary and secondary outcomes, the area under the curve (AUC) for stiffness, pain and function will be compared using a 2-way analysis of variance (ANOVA) with the between factor group (knitting vs control) and within factor time (0 h, 2 h, 4 h, evening). Tukey’s [71] honest significance difference (HSD) will be used to make specific pairwise comparisons. The secondary outcomes, AUSCAN overall, AUSCAN pain, AUSCAN stiffness, AUSCAN function, hand and fingers strength and physical function, self-efficacy, hand physical activity level and adherence, global patient improvement as well as QoL will be compared using a 2-way analysis of variance (ANOVA) with the between factor group (knitting vs control) and within factor time (baseline, 3 wk., 6 wk., 9 wk., 12 wk. and 4-wk Follow-Up). Again, Tukey’s HSD [71] will be used to make specific pairwise comparisons. As a secondary analysis, additional time assessments to 16 weeks will be included in the above analyses to assess follow-up. An alpha significance of 0.05 was chosen for all analyses. Mixed models repeated measured will be used to accommodate missing data. No interim efficacy or subgroup analyses are planned.

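### The primary stiffness outcome is timed from knitting in the outcome section and from awakening elsewhere, and the knitting clock does not exist for controls

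*Protocol article*

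**What the plan says.** **Knitting clock.** Under Self-reported clinical outcomes, stiffness and pain are to be rated before knitting and "after knitting (immediately, 2 h and 4 hours after the 20-min knitting daily morning activity". The next sentence names the primary outcome: "Daily morning stiffness after 2 h knitting daily morning activity will be our primary outcome measure of this protocol". The paragraph on hand activity level in the same section says that the logbook holds a "daily visual analogue scale for morning stiffness and pain intensity before and after knitting".

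**Awakening clock.** The abstract's objective refers to stiffness and "pain relief (secondary outcome) 2 h post-wakening in females". The primary objective at the end of the main Background ends with "osteoarthritis of the hands (HOA) after 2 h post-awakening". Statistical analysis defines the primary outcome through an area under the curve (AUC): "stiffness at 2 h post-awakening from sleep will be assessed each day for 12 weeks". It adds: "Similar AUCs will be calculated for stiffness at 0 h (at awakening), 4 h (post-awakening) and evening".

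**Controls.** Group 2 is on a waiting list and may not attend the knitting sessions (Intervention). Its logbook is described in one sentence: "A similar logbook was created for PA activity other than knitting recording for the participants in the control group 2". Table 1 lists the daily stiffness VAS without limiting it to one arm.

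**Timing of knitting.** The Intervention section places knitting in the morning but gives no interval from waking.

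**The concern.** The primary analysis is a direct comparison of the arms on the 2 h stiffness AUC, so the 2 h must mean the same thing in both arms. Under the outcome section it means nothing for a control. Under the analysis section it is available to everyone. A logbook built around the knitting session in Group 1 and around the day in Group 2 would collect the two arms on different clocks. A later analysis plan could choose an anchor, but it could not recover readings taken at the wrong time.

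Participants are not blinded and complete the logbooks themselves, so the blinded assessor does not protect this outcome. The secondary pain VAS has the same two clocks.

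**Working it through.** **1. The two definitions side by side**

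| | Outcome section | Abstract, objective, analysis section |
|---|---|---|
| Time zero | Knitting session | Awakening |
| Reading times | Before; immediately, 2 h and 4 h after | Awakening, 2 h, 4 h, evening (analysis section) |
| Exists for controls | No | Yes |

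The difference is more than one loose phrase, because the sets of reading times differ too.

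**2. Can the clocks coincide?** Let knitting start *s* minutes after waking. The session lasts 20 min, so the knitting-clock reading falls at *s* + 20 + 120 min after waking. The awakening-clock reading falls at 120 min. The lag is *s* + 20 min, which is at least 20 min even if knitting starts on waking.

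**3. The plan's own figures.** The sample size section uses an effect of 0.8 SD, 80% power and alpha 0.05. A two-sided two-sample t-test (sidedness assumed) needs 25.5, so 26 per group. The plan states 28, at which power is 83.6%. With 5% dropout, 28 / 0.95 = 29.5, so 30 per group as stated. This point does not change the sample size. The feasibility SD of 0.261 is a proportion of the maximum AUC, so on the 10 cm scale it is 2.61 cm, and the planned effect is 0.8 × 2.61 = 2.09 cm. The section says only that patients were assessed at 2 h, without saying from what.

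**4. What a mixed clock could do.** Assume that Group 1 is read on the knitting clock, controls on the awakening clock, there is no treatment effect, and stiffness eases at a constant rate. The article gives neither the lag nor the rate, and does not state that stiffness eases; all three are assumptions.

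Apparent difference = rate × lag. In SD units, divide by 2.61 cm. The rejection rate is that of a two-sided t-test with 30 per arm.

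| Lag | Rate (cm/h) | Difference (cm) | SD units | Rejection rate |
|---|---|---|---|---|
| 20 min | 0.25 | 0.08 | 0.03 | 5.2% |
| 20 min | 0.5 | 0.17 | 0.06 | 5.7% |
| 20 min | 1.0 | 0.33 | 0.13 | 7.8% |
| 1 h | 0.25 | 0.25 | 0.10 | 6.5% |
| 1 h | 0.5 | 0.50 | 0.19 | 11.3% |
| 1 h | 1.0 | 1.00 | 0.38 | 30.9% |
| 2 h | 0.25 | 0.50 | 0.19 | 11.3% |
| 2 h | 0.5 | 1.00 | 0.38 | 30.9% |
| 2 h | 1.0 | 2.00 | 0.77 | 83.1% |

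**5. The floor.** The feasibility mean is 0.188 of the maximum, or 1.88 cm. A 1.00 cm shift would remove 1.00 / 1.88 = 53% of such a mean, and a 2.00 cm shift exceeds it. Many readings on a scale that stops at zero could not fall that far, so the larger entries are not credible at that mean. The feasibility participants all knitted, so the control mean may be higher and the floor less binding. The article does not settle this.

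**The case against.** The strongest reply is that the analysis section, which specifies the primary comparison, gives both arms one clock, and the abstract and objective agree with it. The outcome section is then the outlier, and no section states the mixed clock that produces the bias. This stands. A reader might infer that the trial is biased towards knitting, or that its false-positive rate is several times nominal. The document does not support that: it shows an inconsistent definition, of which different timing in the two arms is one possible consequence.

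Second, nothing in the article says that stiffness eases with time since waking. The Discussion speaks only of the symptom effect of knitting lasting four hours. That also stands, so the direction of any bias is conditional.

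Third, a reader might infer that controls record no daily stiffness at all. That goes too far: their logbook is called similar, and Table 1 restricts only the enjoyment scale to Group 1. What is missing is a stated time zero for their readings.

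Fourth, this is a condensed article, and the interval between waking and knitting or the printed logbook times may be set in the full protocol or the logbooks. That is fair for the missing interval. It does not excuse two conflicting definitions of the primary outcome in the printed text.

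**Conclusion.** The contradiction is established from the text alone and needs no assumption: the primary outcome has two time anchors at least 20 min apart, with different reading schedules, and one anchor is undefined in the control arm. It should be corrected before data are collected.

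Any bias is possible rather than shown. It requires that the arms actually follow different clocks and that stiffness eases during the morning. Under both assumptions it favours knitting. At a 20 min lag it is negligible to small (5.2% to 7.8% false positives for 0.25 to 1 cm/h). It grows with longer lags, but the highest values are limited by the scale floor and should not be quoted as expected. If both arms are read from awakening, this bias does not arise.

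**What to change.** - Reword the primary outcome in Self-reported clinical outcomes as VAS stiffness 2 h after awakening, the anchor already used in the abstract, the objective and the analysis section. Align the secondary pain VAS in the same way.
- Correct the logbook description to match, and print the same reading times in both arms' logbooks: awakening, 2 h, 4 h and evening, as in the analysis section.
- Have every participant record the wake time and the time of each VAS, and Group 1 also the knitting start time.
- Keep the readings taken relative to knitting as descriptive data for Group 1 only.
- State in the sample size section which anchor the feasibility SD refers to.

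The cost is wording and two or three logbook fields, with no extra visits or participants. One limitation remains: on days when knitting starts late, the 2 h reading may precede that day's session. The recorded times will show how often this happens.
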